**Methods/Design:**

An open-label, household-cluster, randomized controlled trial with a two-group parallel design is used. The trial is embedded in a population-based health promotion program, “*Check your Health Preventive Program*”, in which all 30–49 year-old citizens in a Danish municipality are offered a preventive health check. In each arm of the trial, 750 citizens will be recruited (1,500 in total). The primary outcome is cardiorespiratory fitness level assessed by submaximal cycle ergometer testing after one year. An intermediate outcome is the percentage of participants increasing motivation for physical activity behaviour change between baseline and two-weeks follow-up assessed using the Transtheoretical Model´s stages of change. Secondary outcomes include changes from baseline to one-year follow-up in physical inactivity prevalence measured by a modified version of the questions developed by Saltin and Grimby, and in self-rated health measures using the Short-Form 12, Health Survey, version 2.

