### Questionnaire

Prior to the health check, a web-based questionnaire regarding physical activity level [16], motivation for changing physical activity behaviour [17], self-rated health [18], smoking habits [19] and alcohol risk behaviour [20] will be answered. Participants have the opportunity to answer the questionnaire at the RHC, if support is needed.

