### Intermediate outcome

#### Motivation for physical activity behaviour change

Motivation for physical activity behaviour change will be operationalized by conceiving *intention* (to adopt a specific behavioural criterion) as a motivational construct. The Transtheoretical Model will compose the theoretical framework using the stages of change [17]. Stages of change conceptualize behaviour change as a progression through a series of five stages: *precontemplation* (*no intention* to engage in regular physical activity within the next six months), *contemplation* (*intention* to engage in regular physical activity *within the next six month*), *preparation (intention* to engage in regular physical activity *within the next 30 days), action* (regular physical activity behaviour initiated), and *maintenance* (regular physical activity has been performed for 6 month or more) [17, 24]. The three initial stages represent the motivational phase, in which intention is thought to increase [17]. We will consider progression from one of these three stages at baseline to a higher stage assessed two weeks after the health check as a motivational increase [17] and the percentage of participants increasing motivation as the specific outcome. Participants will stage themselves into one of the five stages according to their intention to engage in regular moderate physical activity defined as occurring on 5 or more days a week for at least 30 minutes (or 3 × 10 minutes) [23]. Moderate intensity is defined as producing increased heart rate, but being able to converse.

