### Statistical methods

Statistical analysis will be performed using STATA 12.0 software. Continuous variables are presented as mean ± standard deviation and categorical variables as absolute numbers and relative (%) frequencies. In the comparative analyses Student´s t-test will be used, when comparing means or changes in means of continuous variables and Chi^2^-test or Fisher’s exact t-test, when comparing proportions for categorical variables. Analyses will be adjusted for baseline physical activity. Stratified analyses will be performed on sex and age groups and analysis of motivation will be performed on a subgroup comprising precontemplaters, contemplaters, and preparators at baseline. All analyses will follow the intention-to-treat principle [28]. If appropriate, multiple imputation methods will be applied [29] (using data from social and medical national registries coupled with health check data), and sensitivity analyses will be performed. Moreover, the potential effect of clustering by the GPs will be investigated. The statistical significance level is set at p <0.05.

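### The motivation comparison leaves out baseline stage of change, a value already collected that could add a modest amount of precision

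*Protocol article*

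**What the plan says.** The abstract gives the outcome its role: "An intermediate outcome is the percentage of participants increasing motivation for physical activity behaviour change between baseline and two-weeks follow-up". The section on motivation for physical activity behaviour change defines an increase as "progression from one of these three stages at baseline to a higher stage assessed two weeks after the health check", where the three stages are precontemplation, contemplation and preparation. The result is a single percentage per arm, pooled over the three starting stages.

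The Statistical methods section names Chi-square or Fisher tests "when comparing proportions for categorical variables". It then states: "Analyses will be adjusted for baseline physical activity". It adds: "Stratified analyses will be performed on sex and age groups". For motivation it says only that "analysis of motivation will be performed on a subgroup comprising precontemplaters, contemplaters, and preparators at baseline". Stage of change appears there as a selection rule and nowhere as a covariate or stratum.

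The Questionnaire section places the motivation item in the web questionnaire completed before the health check. The Control group section says that controls answer the same questionnaire. Baseline stage is therefore available in both arms.

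**The concern.** The pooled percentage counts three different events as one. A precontemplator moves up by forming an intention, a contemplator by shortening the horizon of an existing intention, and someone in preparation by actually starting regular activity. It would be surprising if all three were equally likely within two weeks. Where they are not, baseline stage predicts the outcome, and leaving it out keeps between-stage variation in the standard error.

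The named covariate is only a partial substitute. It is a four-level description of typical leisure-time activity. Stage refers to a criterion of moderate activity on five or more days a week, and the three early stages are separated by whether and when a person intends to meet it. A person in the third activity category (sports at least three times a week) could be in any of the three early stages.

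What is at stake is the width of the interval for an outcome that is named in the title and in the first aim. It is analysed on an unstated part of the 1,500 participants, and the sample size was set for fitness, not for motivation.

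**Working it through.** **Inputs.** The article gives no progression rates, no stage mix and no number expected in the early stages. All rates, mixes and analysed numbers below are assumptions. The plan has no figure of its own for motivation to reproduce; its 1,500 concerns the fitness outcome.

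**Formulas.** For stage shares w and progression probabilities p:

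- overall rate: pbar = Σ w·p
- between-stage variance: B = Σ w·(p − pbar)²
- share of outcome variance explained by stage: R² = B / [pbar(1 − pbar)]
- gain in effective sample size: 1/(1 − R²) − 1
- reduction in standard error: 1 − √(1 − R²)
- SD of the error from chance stage imbalance, n per arm: √(2B/n)
- unadjusted standard error of the risk difference: √(2·pbar(1 − pbar)/n)

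**One worked case.** Take rates of 15/30/50% (precontemplation, contemplation, preparation), mix 20/40/40 and n = 300 per arm.

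- pbar = 0.03 + 0.12 + 0.20 = 0.35
- B = 0.2(0.20²) + 0.4(0.05²) + 0.4(0.15²) = 0.008 + 0.001 + 0.009 = 0.018
- R² = 0.018/0.2275 = 0.079
- gain = 1/0.921 − 1 = 8.6%
- imbalance SD = √(0.036/300) = 1.10 points
- unadjusted SE = √(2 × 0.2275/300) = 3.9 points
- SE with the stage component removed = √(3.89² − 1.10²) ≈ 3.7 points, a reduction of 4%

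**Range.** The first four rows use a mix of 30/30/40 (pbar = 0.30, pbar(1 − pbar) = 0.21). The last uses equal thirds (pbar = 0.333, product 0.222). The imbalance SD is at 262 per arm, from 750 × 0.5 × 0.7: half of participants in the early stages, and the article's 30% loss allowance applied to the two-week questionnaire.

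| Rates by stage (%) | B | R² | SE reduction | Sample gain | Imbalance SD (points) |
|---|---|---|---|---|---|
| 30/30/30 | 0 | 0 | 0% | 0% | 0 |
| 25/35/30 | 0.0015 | 0.007 | 0.4% | 0.7% | 0.3 |
| 20/40/30 | 0.0060 | 0.029 | 1.4% | 2.9% | 0.7 |
| 15/45/30 | 0.0135 | 0.064 | 3.3% | 6.9% | 1.0 |
| 10/30/60 | 0.0422 | 0.190 | 10.0% | 23.5% | 1.8 |

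The total unadjusted SE in these rows is about 4 points. Between the last two rows, an R² of 0.122 would give an SE reduction of 1 − √0.878 = 6.3% and a gain of 1/0.878 − 1 = 13.9%.

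**Simulation.** An unadjusted two-group test was compared with a stage-stratified Cochran-Mantel-Haenszel test in 10,000 runs at 262 per arm, ignoring clustering.

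| Rates (%) | Type I error, unadjusted / stratified | Power for a 10-point effect, unadjusted / stratified |
|---|---|---|
| 20/40/30 | 5.1% / 5.2% | 67.4% / 68.4% |
| 15/45/30 | 5.3% / 5.4% | 67.0% / 69.4% |
| 10/30/60 | 5.1% / 5.0% | 66.3% / 73.8% |

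The average estimate was 10.0 points with either method. Omitting stage costs power, little in the first two cases, and does not distort the estimate or the error rate.

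**Comparator.** All these gains are measured against no adjustment. The plan adjusts for baseline activity. If activity correlates with stage, part of the gain is already secured, so every figure above is an upper bound.

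**The case against.** The strongest reply is that nothing here is wrong. The planned comparison is valid, motivation is not the primary outcome, and the choice of a further covariate is a matter of efficiency that a fuller analysis plan may settle. The article does not say that activity is the only covariate that will ever be used. Most of this stands, and it is why the point is minor. What remains is that the article does fix a covariate for its analyses, and for this outcome it names a related variable while using the outcome's own starting value only to select participants.

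Three stronger readings are tempting, and the documents support none of them.

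- **A ceiling.** A reader might infer that baseline stage caps the chance of moving up. The restriction to the three early stages removes that: everyone analysed can rise by at least one stage. What remains is that rates may differ among the three stages, which is plausible but not shown.
- **Bias from chance imbalance.** A reader might infer that an arm with more people in preparation gets a misleading result. Under randomisation such imbalance is sampling error that the standard error already covers. In the worked case it is 1.1 points within 3.9. Adjustment removes that component; it does not correct a bias.
- **A large loss of power.** The gains near 24% need extreme differences between stages. The lower end of the range is zero.

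The Discussion's remark that the early stages have been found to differ supports treating them as distinct. It does not give progression rates, so it cannot narrow the range.

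**Conclusion.** The point holds as one of precision only. Baseline stage is available in both arms, defines the analysed subgroup and is the reference from which the outcome is scored, yet it is absent from the stated comparison. Leaving it out causes neither bias nor a raised type I error.

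Against an unadjusted analysis, adding stage is worth 0% to about 24% in effective sample size. The standard error falls by 0% to 3.3% from flat to strong stage dependence, by 4% with rates of 15/30/50%, and by about 10% in the extreme case. These figures rest wholly on assumed rates, mixes and analysed numbers, ignore clustering, and are upper bounds given the planned activity adjustment. Severity is minor: a free improvement to an intermediate outcome, with no bearing on the primary fitness analysis.

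**What to change.** In Statistical methods, state that motivational increase is compared between arms with baseline stage of change as a three-level factor, in addition to baseline physical activity. A logistic model standardised to a risk difference would do this and keep the effect on the percentage scale in which the outcome is defined. Add a table of progression by arm within each baseline stage, which would also show whether any effect lies in forming intentions or in starting activity.

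The definition of motivational increase and the analysed subgroup stay as written. The cost is one sentence and one table. No new data are needed, because stage must be known to form the subgroup, and participants carry no extra burden. The choice should be fixed before outcome data are examined.

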### Participants and settings

In the CHPP, all citizens living in the municipality of Randers aged 30–49 years per 1^st^ of January 2012 (n =26,216) were identified in the Danish Civil Register, in which a permanent and unique identification number is assigned to every Danish inhabitant at birth and to residents on immigration. The identified population was randomized into five equal groups, one for each year of the CHPP [6]. Citizens randomized for group three (n =5,249) are considered eligible for the present trial (Figure 1). A single exclusion criterion for not receiving an invitation in the CHPP is terminal illness as reported by the general practitioners (GPs) [6]. Invitations are dispatched continuously by mail and include information about the CHPP and a prefixed appointment for a health check. This appointment can be accepted, altered or rejected via phone or internet. If no response, a reminder with a new appointment is sent after 7 days and again after three weeks [6]. Randomization in the present trial is conducted prior to dispatching the invitations. The enrolment proceeds continuously, until 750 participants in each arm of the trial have received a health check and consented for data to be used scientifically. Health checks and health behavioural courses will take place at Randers Health Centre (RHC) and health consultations at the citizen´s GP.

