### Randomization and implementation

Randomization is handled by a data-manager with no scientific involvement. The eligible population for this trial was defined by the CHPP randomization, which was performed on clusters defined by households based on addresses obtained from the Danish Civil Register [6]. Using the same index individual per household, citizens randomized to group three in the CHPP will be further randomized by household to either intervention or control in the present trial (Figure 1). In practice, every second week will be scheduled for intervention group participants and the remaining weeks for control group participants. Group assignment will be maintained regardless of changes in the initially assigned appointment. Implementation and management of the booking-system is handled by a data-manager. The intervention, the outcomes, group assignment, and the future outcome assessments in this trial are unrevealed in the invitation for the CHPP. The health behavioural courses and the health consultations will be carried out unblinded due to the real-life setting. At the one-year follow-up, the personnel assessing the outcomes will be independent and blinded to group allocation.

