### Sample size

The sample size is estimated to be 1,500 participants in total. This sample size allows for a categorical analysis of fitness level and is calculated on the basis of the following assumptions: 1:1 randomization, false positive error rate of 0.05, power of 0.8, intracluster correlation coefficient of 0.05 and categorical analysis with a power to detect a difference of 10% in the prevalence of very low fitness between the study groups. We determined this 10% difference to be clinically meaningful based on expert opinions and criteria employed in other research [26]. The intracluster correlation coefficient was included to reflect a possible clustering effect of the GPs (n =46), which is seldom greater than 0.05 in primary care settings [27]. The estimated sample size accounts for a 30% loss to follow-up.

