### Strengths and limitations

The present trial holds several strengths. Participants will be recruited directly from the community receiving no screening prior to inclusion. Thereby, the generalizability will not be restricted in advance to certain at-risk populations such as physically inactive people or people with chronic diseases. Moreover, the risk of diluting an intervention effect by prerandomization research activities [12] is omitted. The objective measure of fitness provides effect estimates with high internal validity. Furthermore, the one-year follow-up period and the intention-to-treat approach form the basis of high external validity.

Some important limitations also deserve consideration. Firstly, although the Astrand method of predicting fitness has been shown valid at a group-level [44], the risk of misclassification exists at the individual level [43]. Fitness will be assessed identically in the two groups being compared. Hence, any misclassification would be non-differential, and the resulting bias would lead towards null. Secondly, contamination may occur across social groups and in the community. In recent years, the municipality of Randers has implemented health promotion initiatives, which may impact on trial outcomes leading to further attenuation of the intervention effect. Thirdly, blinding of health professionals and GPs is impossible in a pragmatic trial such as this. Consequently, the risk of performance bias cannot be ruled out. Finally, a full application of the intention-to-treat principle requires complete outcome data for all randomized subjects [45]. This is rarely possible in pragmatic trials, in which losses to follow-up are common and introduce a risk of selection bias [45]. Nevertheless, no consensus exists about how missing outcome data should be handled in intention-to-treat analyses [45]. We will address potential bias by imputing missing outcome data and performing sensitivity analyses.

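### The intention-to-treat claim does not describe the analysed set: households are randomised before invitation, but only citizens who then attend and consent enter the trial

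*Protocol article*

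**What the plan says.** - **Pool.** Participants and settings: "Citizens randomized for group three (n =5,249) are considered eligible for the present trial".
- **Allocation.** Randomization and implementation: "citizens randomized to group three in the CHPP will be further randomized by household to either intervention or control in the present trial". On timing, Participants and settings says "Randomization in the present trial is conducted prior to dispatching the invitations".
- **Who enters the trial.** The same section has enrolment run "until 750 participants in each arm of the trial have received a health check and consented for data to be used scientifically". The legend to Figure 1 repeats this rule.
- **Sample size.** "The sample size is estimated to be 1,500 participants in total". This counts the same attending and consenting people, and the 30% allowance for loss applies to them.
- **Analysis principle.** Statistical methods: "All analyses will follow the intention-to-treat principle". Imputation, where used, draws on national registry data linked to health check data.
- **What is drawn from it.** Strengths and limitations: "the one-year follow-up period and the intention-to-treat approach form the basis of high external validity". The same section accepts that full intention-to-treat needs outcomes on everyone randomised, but goes on to discuss only participants lost during follow-up.
- **Safeguards.** Randomization and implementation keeps the intervention, the group and the later assessments out of the invitation. It also keeps the assigned group if an appointment is moved, and gives the booking system to a data manager.

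**The concern.** Attendance and consent both come after randomisation, and both decide who is analysed. Randomised citizens who do not attend, or who attend and decline data use, have no place in any analysis described. The article therefore claims a property that its enrolment rule rules out.

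Two things are at stake. The first is scope: the trial can estimate the effect of adding a fitness test among people who attend and consent, but intention-to-treat cannot support a claim of external validity beyond them. The second is comparability: randomisation protects the comparison among consenting attenders only if attendance and consent do not depend on the arm. The planned imputation does not help, because it relies on health check data that non-attenders do not have and is aimed at outcomes lost among those enrolled.

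**Working it through.** **1. The stated sample size.** The 1,500 cannot be reproduced uniquely, because the control prevalence of low fitness and the cluster size used are not given. It can be reached. Inputs from Sample size: "1:1 randomization, false positive error rate of 0.05, power of 0.8, intracluster correlation coefficient of 0.05", a 10-point difference, 46 GPs and 30% loss. Assume a two-sided test and 25% versus 15%:

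- n per arm = [1.96·√(2·0.20·0.80) + 0.8416·√(0.25·0.75 + 0.15·0.85)]² / 0.10² = 250
- mean number with outcome per GP = 1,500·0.70/46 = 1,050/46 = 22.8; design effect = 1 + (22.8 − 1)·0.05 = 2.09
- total = 2 × (250·2.09/0.70) ≈ 1,494

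The figure is not disputed here. It counts attending consenters, so renaming the set leaves the planned power unchanged.

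**2. Share of the pool analysed.** If all of group three is randomised, 1,500/5,249 = 28.6% are in the trial and 71.4% are outside it. After 30% loss, 1,050/5,249 = 20.0% have a one-year outcome.

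**3. What the 71.4% contains.** Uptake (attendance and consent together) is not given, so it is varied, taken as equal in both arms. Invited = 1,500/uptake; lost after invitation = invited − 1,500; never invited = 5,249 − invited.

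| Assumed uptake | Invited | Lost to non-attendance or non-consent | Never invited |
|---|---|---|---|
| 30% | 5,000 | 3,500 | 249 |
| 40% | 3,750 | 2,250 | 1,499 |
| 50% | 3,000 | 1,500 | 2,249 |
| 60% | 2,500 | 1,000 | 2,749 |
| 70% | 2,143 | 643 | 3,106 |
| 80% | 1,875 | 375 | 3,374 |

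Non-attendance and non-consent would remove more than half of the 5,249 only if invited − 1,500 exceeded 2,624.5. That means more than 4,124.5 invited, or uptake below 1,500/4,124.5 = 36.4%. They would remove more than half of those invited only if uptake were below 50%.

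**4. What differential inclusion would do, if it occurred.** Suppose there is no true effect, the prevalence of low fitness is p in both arms, and people with low fitness are under-represented in the intervention arm's analysed set by a relative fraction d. Then the apparent intervention prevalence is p(1 − d)/[p(1 − d) + (1 − p)]. For p = 25%:

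- d = 5%: 0.2375/0.9875 = 24.05%, a shift of −0.9 points
- d = 10%: 0.225/0.975 = 23.08%, −1.9 points
- d = 20%: 0.20/0.95 = 21.05%, −3.9 points

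The same formula at d = 10% gives 0.135/0.985 = 13.7% for p = 15% (−1.3 points) and 0.315/0.965 = 32.6% for p = 35% (−2.4 points). These compare with a target difference of 10 points. Both p and d are assumptions, and no figure in the article supports a value of d other than zero.

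**The case against.** The strongest reply is that the trial asks what a fitness test adds to a health check, a question about attenders. Non-attenders receive neither version of the check, and the invitation does not reveal the arm. Leaving them out then limits generalisability without biasing the comparison, and the label is a matter of wording. Much of this stands: concealment and the fixed assignment make arm-dependent attendance unlikely. It does not rescue the text, because the article itself sets the standard of outcomes on everyone randomised, and then claims the principle and builds external validity on it.

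A reader might infer more than the article supports:

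- **That attendance and consent exclude most of those randomised.** The 71.4% mixes them with citizens never invited once the quota was full, and stopping at a quota is not selection by attendance or consent.
- **That the arms are selected differently.** Nothing shows this. Consent is the main open route, because the check is open-label and its results are given at its end. The article does not say when consent is taken, and it may leave such detail to fuller documents, so that silence is not a defect in itself.
- **That people barred from the fitness test drop out of the intervention arm.** Fitness testing bars them from the test only. The enrolment rule counts a received check and consent.
- **That members of a household tell one another the arm, or that the quota hides unequal uptake.** The first is conjecture. The second fails if the numbers invited are reported by arm, and the article commits to CONSORT.

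**Conclusion.** The point holds in a limited form. The claim in Statistical methods is wrong as written, because the set is defined by two events after randomisation. Strengths and limitations is wrong to rest external validity on intention-to-treat and to treat loss to follow-up as the only departure. The conclusion can cover consenting attenders, who are 28.6% of the pool if all 5,249 are randomised. How much of the rest reflects non-attendance or non-consent is unknown without an uptake figure.

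Bias in the primary comparison is possible but not shown. Under the assumed 25% prevalence it would be 0.9 to 3.9 points for a relative under-representation of 5% to 20%. The correction is worth making because it changes what the trial may conclude and because attendance and consent by arm can be checked directly.

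**What to change.** 1. **Statistical methods.** Replace the claim with a modified intention-to-treat set: citizens randomised who attended a health check and consented, analysed in the group assigned to their household, including intervention attenders who could not take the baseline fitness test.
2. **Strengths and limitations.** Limit the conclusion to consenting attenders, remove intention-to-treat as a basis for external validity, and add non-attendance and non-consent to the stated departures.
3. **Reporting.** Give the numbers randomised, invited, attending and consenting by arm. Compare attendance and consent between arms allowing for household clustering. If they differ, add a sensitivity analysis, for example one weighted for inclusion.
4. **Consent, as a secondary safeguard.** If written consent for data use is not already obtained before the arm or the fitness result is known, obtain it at that point. If it already is, say so.

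The cost is two changes of wording, a flow table by arm, one added comparison and possibly a change in when consent is taken. The downside is a less favourable validity claim and a little more analysis. The sample size is unaffected.

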## Methods

### Trial design

The trial is as an open-label, household-cluster randomized controlled trial with a two-group parallel design. The trial is nested in the ongoing health promotion program entitled *Check your Health Preventive Program* (CHPP) [4, 6]. The CHPP is carried out during the five-year period 2012 to 2017. The present trial will be conducted in 2014 to 2016, including a follow-up period of one year.

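### Households are randomised, but the named tests assume independent individuals and the only clustering considered is by GP, so the 5% test can exceed 5%, probably by a modest amount

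*Protocol article*

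**What the plan says.** The Trial design section of the protocol article describes a "household-cluster randomized controlled trial with a two-group parallel design". Randomization and implementation confirms the unit: citizens in group three of the parent programme "will be further randomized by household to either intervention or control in the present trial".

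Eligibility and recruitment are counted in people. Participants and settings states: "Citizens randomized for group three (n =5,249) are considered eligible for the present trial". Enrolment runs "until 750 participants in each arm of the trial have received a health check and consented for data to be used scientifically". One address can therefore supply more than one participant, always in the same arm.

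Statistical methods says that Student's "t-test will be used, when comparing means or changes in means of continuous variables", and names Chi-squared or Fisher's exact test for proportions. It adds adjustment for baseline physical activity without naming a model, and sets significance at p <0.05. On clustering it says only: "Moreover, the potential effect of clustering by the GPs will be investigated".

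The Sample size section includes an intracluster correlation of 0.05, which it attributes to the 46 GPs. The household appears in neither the sample size nor the analysis.

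**The concern.** A test is valid under cluster randomisation only if its standard error reflects the unit that was randomised. The t-test, Chi-squared test and Fisher's exact test treat each participant as a separate draw. Two housemates always receive the same allocation. If their outcomes are also alike, they carry less information about the arm difference than two unrelated people.

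The plan shows awareness of clustering but attaches it to the GP. Allocation is by household, so one GP can have patients in both arms. Looking into GP clustering does not replace accounting for the household.

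At stake is whether the p <0.05 criterion is a true 5% test for the primary fitness comparison, and to varying degrees for the intermediate and secondary outcomes.

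**Working it through.** **1. The plan's own figure.** The 1,500 cannot be reproduced uniquely, because the base prevalence and the GP cluster size used are not stated. It can be reached with a GP design effect alone, assuming a two-sided test:

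- Assume 25% versus 15% low fitness, alpha 0.05 and power 0.80. This needs 250 per arm.
- Analysed participants after 30% loss: 1,500 × 0.70 = 1,050. Per GP: 1,050/46 = 22.8.
- GP design effect: 1 + (22.8 − 1) × 0.05 = 2.09.
- Total: 2 × 250 × 2.09 / 0.70 ≈ 1,494.

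Other combinations come equally close. With 20% versus 10% and 1,500/46 per GP the total is 1,468. With 30% versus 20% and 750/46 per GP it is 1,484. The 1,500 is plausible, and no household term is needed to reach it.

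**2. Household design effect.** Let *f* be the share of analysed participants who have an analysed housemate, with at most two analysed per household, and let ρ be the household intracluster correlation. Neither is in the document, so both are assumptions.

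- Participant-weighted mean cluster size: Σm²/Σm = (1 − f) × 1 + f × 2 = 1 + f.
- Design effect: DE = 1 + f × ρ.
- Actual two-sided type I error of the naive 5% test: 2 × [1 − Φ(1.96/√DE)].
- Shortfall in interval width: 1 − 1/√DE.

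| f | ρ | DE | Type I error | Interval too narrow by | True coverage |
|---|---|---|---|---|---|
| 0.2 | 0.1 | 1.02 | 5.2% | 1% | 94.8% |
| 0.3 | 0.2 | 1.06 | 5.7% | 3% | 94.3% |
| 0.5 | 0.2 | 1.10 | 6.2% | 5% | 93.8% |
| 0.5 | 0.3 | 1.15 | 6.8% | 7% | 93.2% |
| 1.0 | 0.5 | 1.50 | 11.0% | 18% | 89.0% |

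The last row is a bound, not an expectation. A simulation with household randomisation and 1,050 analysed participants agreed: 5.0% with no pairs, 5.7% at f = 0.3 and ρ = 0.2, 6.6% at f = 0.5 and ρ = 0.3, and 10.8% at the bound.

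**3. How large can f be?** The plan allows for 30% loss. If housemates are lost independently, a retained participant's housemate is retained with probability 0.70, so f is at most 0.70 × the share paired at baseline. Complete pairing at baseline would leave f = 0.70. The range 0.2-0.5 corresponds to baseline pairing of 0.2/0.70 = 29% to 0.5/0.70 = 71%. Higher values need near-universal pairing, strongly shared dropout, or both.

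**4. Power.** With 525 analysed per arm and a household design effect of 1.15 alone, power for 25% versus 15% is about 97%, and for 50% versus 40% about 86%. The household effect (1.02-1.15) is far smaller than the GP allowance of about 2.09. The defect therefore concerns the standard error, not the number recruited.

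**The case against.** **The inflation is conditional.** A reader might infer that the error rate is certainly above 5%. The document does not support that. It gives no household size and no within-household correlation, and if almost every household supplies one participant the effect vanishes. This limits the claim to a conditional one.

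**Not every comparison is equally exposed.** A reader might apply one design effect to all outcomes. The sex-stratified analyses separate mixed-sex couples. The motivation analysis keeps only people in the first three stages of change at baseline, so a pair counts only if both members are in those stages. Adjustment for baseline activity may also remove part of any shared-habit correlation. This stands: these analyses are probably less affected.

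**A regression is implied.** The named tests cannot adjust for baseline activity, so some model must be intended, and a fuller document may specify its variance estimator. This stands in part. However, covariate adjustment does not by itself account for household correlation. The article also does not leave clustering open: it names one level, and not the randomised one.

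**GP-level handling might absorb it.** If housemates share a GP, robust standard errors at GP level would also cover household correlation. The article neither says that housemates share a GP nor commits the primary test to any correction.

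**The sample size already carries a design effect.** True, and power is not threatened. Recruiting more people does not repair a standard error computed as if they were independent.

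**One participant per household?** The index individual in Randomization and implementation is the device for randomising by household. Nothing restricts invitation or analysis to that person.

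**Conclusion.** The mismatch is in the text: households are randomised, the named tests assume independent individuals, and the only clustering considered is at a level that was not randomised. The direction is anti-conservative whenever some households contribute two or more analysed participants with positively correlated outcomes.

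The size rests on assumptions. For f = 0.2-0.5 and ρ = 0.1-0.3, with at most two analysed per household, the type I error is about 5.2-6.8% and intervals are about 1-7% too narrow. The article states only a p-value criterion, so the interval figure applies to any interval built from the same standard error.

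This should be fixed before analysis because it touches the primary comparison and the remedy is cheap. It does not undermine the trial. Under these assumptions the inflation is roughly 0.2 to 1.8 percentage points, and the omission does not itself bias the point estimate.

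**What to change.** In Statistical methods, replace the t-test and Chi-squared or Fisher comparisons as the primary analyses with regression models that use cluster-robust standard errors at household level:

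- a linear model for mean fitness and for the changes in SF-12 scores;
- a binomial or logistic model for low fitness, increase in motivation and physical inactivity, with the choice fixed in advance because it sets the effect measure.

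Include the planned adjustment for baseline physical activity in these models, which the named tests cannot do. Keep GP clustering as a sensitivity analysis.

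One method should be named. Random-intercept models and GEE are not interchangeable alternatives for the binary outcomes: a random-intercept logistic model gives a conditional odds ratio and GEE a marginal one. With clusters of mostly one or two people, the random-intercept variance would also be poorly estimated.

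The cost is a change of wording and a cluster option in the software. The household identifier already exists from randomisation. Under the assumptions above, intervals widen by a factor of √1.02 to √1.15, that is by about 1% to 7%.
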